## Abstract

**Background:**

Frail elderly persons living at home are at risk for mental, psychological, and physical deterioration. These problems often remain undetected. If care is given, it lacks the quality and continuity required for their multiple and changing problems. The aim of this project is to improve the quality and efficacy of care given to frail elderly living independently by implementing and evaluating a preventive integrated care model for the frail elderly.

**Methods/design:**

The design is quasi-experimental. Effects will be measured by conducting a before and after study with control group. The experimental group will consist of 220 elderly of 8 GPs (General Practitioners) who will provide care according to the integrated model (The Walcheren Integrated Care Model). The control group will consist of 220 elderly of 6 GPs who will give care as usual. The study will include an evaluation of process and outcome measures for the frail elderly, their caregivers and health professionals as well as a cost-effectiveness analysis. A concurrent mixed methods design will be used. The study population will consist of elderly 75 years or older who live independently and score a 4 or higher on the Groningen Frailty Indicator, their caregivers and health professionals. Data will be collected prospectively at three points in time: T0, T1 (3 months after inclusion), and T2 (12 months after inclusion). Similarities between the two groups and changes over time will be assessed with t-tests and chi-square tests. For each measure regression analyses will be performed with the T2-score as the dependent variable and the T0-score, the research group and demographic variables as independent variables.

**Discussion:**

A potential obstacle for this study will be the willingness of the elderly and their caregivers to participate. To increase willingness, the request to participate will be sent via the elders’ own GP. Interviewers will be from their local region and gifts will be given. A successful implementation of the integrated model is also necessary. The involved parties are members of a steering group and have contractually committed themselves to the project.

**Trial registration:**

Current Controlled Trials ISRCTN05748494

## Background

With an aging population, caring for the increasing number of the frail elderly is a challenge for the Dutch healthcare system [1,2]. The frail elderly are those with a disease or infirmity associated with advanced age, which is manifested by demonstrable mental, psychological, emotional or physical dysfunction to the extent that the person is incapable of adequately providing for his or her own health and personal care presently or in the near future [3,4]. In 2010, 16% (2.6 million) of the Dutch population was 65 years or older, of which 10% was 75 years or older and 7% was 80 years or older [5]. Of the elderly population in 2010, 25% were considered frail. As a result of reduced mortality rates and the demographic shift, there will be a higher frail population in need of long-term care in the near future. The percentage of the frail elderly is estimated to increase to 68% in 2030 [6]. In the meantime, the demand for services already strains the professional workforce and caregiver burden [7-9].

The frail elderly are an important group within the elderly population because their diminished compensation capacities make them, their caregivers, and society most able to benefit from changes in social and healthcare arrangements [10,11]. Due to their complex and continuously changing health and social problems, the frail elderly need a wide range of services over a long period of time [12]. However, the reluctance of the frail elderly to report their growing impairments to their doctors impedes interventions at a stage when preventive care could diminish further mental, psychological or physical deterioration [13]. Approximately 30% of the Dutch frail elderly receive no domestic, personal, home or private care [14]. They solely rely on their own judgment or that of their caregivers for seeking help or for performing their daily activities. Timely recognition of unmet needs can avoid crisis situations or the overburdening of the caregiver. It can also improve social wellbeing [15-17].

Changes also occur in the attitudes of the elderly toward care. These changes also necessitate changes in the organization of care. The frail elderly no longer silently accept the care that they are given and now demand their care meets their needs. Patient-centeredness has become a legitimating base for healthcare provision and has been reinforced by laws that strengthen patient's rights. These laws also force providers to provide the care that the elderly want and need at the right time and place [5,18-20]. A supply-oriented approach and the fragmentation in the organization of the elderly care today inhibit progress on this issue. Service is still often characterized by a lack of continuity and coordination on the behalf of involved providers. Responsibility for the whole continuum of care is absent and results in inefficient and ineffective care [21,22]. The specific needs of the frail elderly and their caregivers, budget restraints and patient-centered views call for new and more effective organizational structures.

The integration of health services and social services for the frail elderly has gained tremendous attention as a means to accomplish this. There is a widespread belief that the integration of these will enhance satisfaction, quality of life, efficiency, and health outcomes and will also decrease costs [23-26]. The rationale behind this stems from the fact that a single service provider is usually unable to respond to all the needs. This prohibits efficiency in the delivery process. To meet the multiple needs of the frail elderly in an efficient and effective manner, some claim that numerous service providers will need to combine their efforts in a coordinated manner [27-29]. There is also mounting evidence that confirms beliefs that the development of integrated care arrangements can be cost effective and enhance quality [30-38].

Though widely acknowledged and pursued, the implementation and evaluation of integrated services for the frail elderly has not yet reached its full potential. Much is still unknown regarding how services can be integrated and the effects of integration. In this study, a new integrated model for the frail elderly, the Walcheren Integrated Care Model, will be developed and evaluated. Walcheren refers to the region in the Netherlands where the study takes place. The Walcheren Integrated Care Model is in accordance with scientific evidence and addresses the design elements that affect the quality of care. It has an umbrella organizational structure involving case management, multidisciplinary teams, protocols, consultations, and patient files. It will be an organized provider network with evidence-based needs assessments [29,32,33]. All elements are embedded in the model. However, more types of health professionals participate in the model than other studies have previously investigated. General practitioners, geriatricians, home health care workers, paramedics, social workers, pharmacists, and mental health care professionals all take part in the designed model. In contrast with other models, this model also contains a preventive element: a screening tool to detect frailty in the elderly. Finally, the model is being evaluated on a broader range to obtain a comprehensive evaluation and determine possible trade-offs between effects.

This article describes the study design of the evaluation of the Walcheren Integrated Care Model compared with traditional care. The development and evaluation of the model are part of the National Care for the Elderly Program (NPO), which is funded by the Netherlands Organization for Health Research and Development (ZonMW; project number 313030201).

### The intervention: the Walcheren integrated care model

The Walcheren Integrated Care Model (WICM) is a comprehensive integrated model for the detection and assessment of needs and the assignment and evaluation of care for independently living frail elderly. The model comprises ten elements: a screening tool for the detection of frailty in the elderly, a single entry point, an evidence-based comprehensive need assessment tool, a multidisciplinary individualized service plan, case management, multidisciplinary team consultation and meetings, protocol-led care assignment, a steering group, task specialization and delegation, and a chain computerization system (see Figure 1).

**Figure 1 F1:**
[figure not shown]
The Walcheren Integrated Care Model (WICM).

The frail elderly aged 75+ years are identified by their general practitioner (GP) by the Groningen Frailty Indicator (GFI), a tool for the detection of frailty. The GFI is a 15-item questionnaire that measures decreases in physical, cognitive, social, and psychological functioning. Scores can range from 0 to 15 [39,40]. A geriatric nurse practitioner that works at the GP practice sends the GFI questionnaire to the homes of the elderly and then contacts them by telephone if they do not respond. When necessary, elderly are helped at home to complete the questionnaire. A geriatric nurse practitioner and GP calculate the GFI score. Elderly with a GFI ≥4 are identified as frail and assigned to a case manager. The geriatric nurse practitioner is the case manager for elderly with single needs. A secondary line geriatric nursing specialist is assigned as case manager if the needs are multiple or of a complex nature.

The case manager then sets up a meeting with the elderly to assess their needs with the EASYcare instrument. EASYcare is an evidence-based comprehensive need assessment instrument that assesses (instrumental) activities of daily life, cognition, and mood. It also contains a module for converting care requirements relating to welfare, residence, and care into treatment goals [41]. The goals are drawn up in consultation with the elderly and their caregivers. Explicit attention is paid to the necessary support and guidance of the caregivers. The results of the assessment are described by the case manager in an individualized care plan. The case manager also creates a proposal for required care and care objectives.

The proposed plan is then discussed in a multidisciplinary meeting led by the GP. Depending on treatment goals, the meeting is also attended by other health professionals who may be needed. During the meeting, a multidisciplinary care plan will be approved, actions and care paths will be discussed, and agreements will be made about the care to be deployed and the activities of all persons involved. The treatment plans of each professional are included in the care plan. The GP harmonizes the care plan with the elderly and their caregiver and obtains permission for its implementation. A chain computerization system accessible by the health professionals involved will be used for the multidisciplinary care plan. The professionals will automatically receive an email in the event of changes in use of care or a transfer.

The case manager is responsible for admittance to the required services, the planning and coordination of care delivery, and periodical evaluation of the care plan. Thus, the case manager arranges obligatory need assessment, monitors the elderly at least every six months for one year, and supports the multidisciplinary team by arranging meetings and streamlining the necessary exchange of information. The responsibilities and activities of the involved professionals and case manager are formalized in agreed protocols with predefined modes of referral and collaboration. During the process, the GP practice functions as a single entry point. It is the gate through which elderly and professionals can access the expertise and services of all health and social care professionals and organizations. The GP and case manager work in close collaboration to ensure timely and correct care assessment and provision. To be able to fulfill their tasks, the GPs must have completed an executive training in geriatric care, a course in GP consults and EASYcare training. The case managers must have successfully attended the EASYcare training and a course in case management.

## Methods and design

### Aim

The aim of the project is to improve the quality and efficacy of care given to frail elderly living independently by their caregivers and health professionals. It seeks to do this by implementing, evaluating, and disseminating an integral care model for the frail elderly. Living independently is defined as living at home or in a sheltered accommodation without receiving other forms of integrated care. The research questions for the evaluation study is as follows: What are the effects of the Walcheren Integrated Care Model on the caregivers, health professionals, the organization of care and the healthcare costs for the frail elderly, and what are the effects on the quality and efficacy of the care given to the frail elderly living independently?

### Study design

The study has a quasi-experimental design in which the effects will be measured before and after the study. A control group will also be used. The study includes an evaluation of process and outcome measures for the frail elderly, their caregivers, and health professionals, as well as a cost-effectiveness analysis. To evaluate the effects, a combination of qualitative and quantitative research methods will be used. (See Tables 1, 2, 3 and 4). The study protocol has been reviewed by the medical ethics committee of the Erasmus Medical Centre, Rotterdam, the Netherlands, under protocol number MEC-2013-058. They waived further examination as the rules laid down in the Medical Research Involving Human Subjects Act did not apply.

**Table 1 T1:** Outcome measures and data collection frail elderly

**Outcome and instrument**	**Method**	**Data collection time**		
		**T0**	**T1**	**T2**
*Primary outcomes*				
**Quality of life**				
ICECAP	Interview elderly	x	x	x
EQ-6d	Interview elderly	x	x	x
SF-36	Interview elderly	x	x	x
Cantril’s self-anchoring ladder	Interview elderly	x	x	x
*Secondary outcomes*				
**Perceived health**				
SF-36	Interview elderly	x	x	x
**Social functioning**				
SF-36	Interview elderly	x	x	x
**Mental well being**				
SF-36	Interview elderly	x	x	x
**Physical functioning**				
KATZ-15	Interview elderly	x	x	x
**Health care use**				
Self-reported	Interview elderly	x	x	x
Reported by GP	File research	x	x	x

**Table 2 T2:** Outcome measures and data collection caregivers

**Outcome and instrument**	**Method**	**Data collection time**		
		**T0**	**T1**	**T2**
**Perceived health**				
SF-36	Interview caregiver or mailed questionnaire	x	x	x
**Objective burden**				
Short version iBMG	Interview caregiver or mailed questionnaire	x	x	x
instrument objective burden informal care				
**Subjective burden**				
Carer-Qol	Interview caregiver or mailed questionnaire	x	x	x
SRB	Interview caregiver or mailed questionnaire	x	x	x
CSI+	Interview caregiver or mailed questionnaire	x		x
Perseverance time	Interview caregiver or mailed questionnaire	x		x
ASIS	Interview caregiver or mailed questionnaire	x		x
**Quality of life**				
SF-36	Interview caregiver or mailed questionnaire	x	x	x
Cantril’s self-anchoring ladder	Interview caregiver or mailed questionnaire	x	x	x
**Use of community services**				
Self-reported	Interview caregiver or mailed questionnaire	x	x	x
CSAI	Interview caregiver or mailed questionnaire	x		x

**Table 3 T3:** Outcome measures and data collection health professionals

**Outcome and instrument**	**Method**	**Data collection time**		
		**T0**	**T1**	**T2**
**Knowledge**				
Self-constructed VAS	Mailed questionnaire	x		x
**Job satisfaction**				
Job satisfaction scale	Mailed questionnaire	x		x
**Subjective burden**				
SRB	Mailed questionnaire	x		x
**Objective burden**				
Self-reported by elder	Interview elderly	x	x	x
Self-reported by professional	Time tracking form	x	x	x
Reported by GP	File research	x	x	x

**Table 4 T4:** Process measures and data collection

**Outcome and instrument**	**Method**	**Data collection time**		
		**T0**	**T1**	**T2**
**Degree of integration**				
Self-constructed questionnaire	Mailed questionnaire	x		x
**Satisfaction health professionals**				
Self-constructed questionnaire	Mailed questionnaire	x		x
Relational coordination Survey	Mailed questionnaire	x		x
Self-reported satisfaction	Diaries	x	x	
	Interviews			x
	Focus groups	x	x	x
**Satisfaction frail elderly**				
CQ-index	Interview elderly	x	x	x
Self-constructed questionnaire	Interview elderly	x	x	x
**Satisfaction caregiver**				
CQ-index	Interview caregiver or mailed questionnaire	x	x	x
Self-constructed questionnaire	Interview caregiver or mailed questionnaire	x	x	x

### Power calculation

We will include 220 elderly in both the experimental and control group. We expect a 10% loss to follow-up (due to mortality, re-housing, impossibility or unwillingness to participate further) between inclusion and T1 and a 20% loss between T1 and T2. The sample is sufficient to detect changes in our primary measure of quality of life. Assuming an average effect size of 0.5 and significance of 5%, this gives a power of 0.997. If we assume a small effect size of 0.3 with a significance of 5%, this still supplies sufficient power at 0.837. Interfering variables will also play a role. At an average effect size (f2) of 0.15 and significance of 5%, assuming five independent variables, the power is 0.97. Even with 15 independent variables, the power remains sufficient at 0.856.

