##### SF-36

Questions based on the SF-36 on perceived current quality of life and the quality of life compared with one year ago will be used.

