### Data analysis

The experimental and control groups will be described at every point in time with descriptive statistics. Similarity of characteristics between the two groups will be assessed with t-tests, chi-square tests, and Fisher’s exact tests. Bivariate analyses and regressions with the demographic characteristics will determine multicollinearity and correlations with the process and outcome measures. All analyses will be controlled for differences in baseline characteristics and demographic characteristics. For the self-constructed questionnaires, factor analyses and reliability analyses will be performed to determine construct validity. To determine changes over time, t-tests will be performed for each process and outcome measure. For each measure, regression analyses will be performed with the T2-score as the dependent variable and the T0-score, the research group (experimental or control), and demographic variables as independent variables. With subgroup analyses, potential variation between study results between subgroups will be analyzed.

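### Four quality-of-life instruments are listed as primary and analysed separately, but the power statement covers one unnamed measure at the full 5%

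*Protocol article*

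**What the plan says.** Table 1 (Study design section) has the plural heading "Primary outcomes". Quality of life is the only domain under it, with four instruments: ICECAP, EQ-6d, SF-36 and "Cantril’s self-anchoring ladder". All four are marked for T0, T1 and T2. The SF-36 entry is described later as two items: "Questions based on the SF-36 on perceived current quality of life and the quality of life compared with one year ago will be used".

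The Power calculation section uses the singular: "The sample is sufficient to detect changes in our primary measure of quality of life". It does not say which instrument is meant. It continues "Assuming an average effect size of 0.5 and significance of 5%, this gives a power of 0.997" and "If we assume a small effect size of 0.3 with a significance of 5%, this still supplies sufficient power at 0.837". The regression figures that follow also use 5%: "At an average effect size (f2) of 0.15 and significance of 5%, assuming five independent variables, the power is 0.97". No other significance level appears in the article.

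The Data analysis section specifies one regression per measure, with the T2 score as the outcome and the T0 score, study group and demographic variables as predictors. It also says: "To determine changes over time, t-tests will be performed for each process and outcome measure". It ranks no instrument first, defines no composite and gives no rule for what counts as a positive primary result.

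**The concern.** The list of primary outcomes and the power statement do not describe the same thing. One gives four endpoints, each with its own regression; the other gives the power of a single test. Followed as written, the plan yields four unranked T2 group coefficients, any of which could be presented as the primary result once the data are seen.

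Two things are at stake. The chance of a false positive claim on the primary outcome may exceed 5%. And the power called sufficient at a small effect applies to a single test at the full 5%, not to four tests that share it. The study is not randomised, and its Discussion accepts that confounders may be missed, so a primary outcome fixed in advance is one of the few protections it has.

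**Working it through.** **Inputs from the article**
- Primary instruments: 4 (Table 1).
- Significance level: 5%, sidedness not stated (Power calculation).
- Enrolled: 220 per group. Losses: 10% to T1, then 20% between T1 and T2 (Power calculation).
- Effect sizes 0.5 and 0.3, stated power 0.997 and 0.837 (Power calculation).

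**Assumptions not in the article**
- The 5% of the power section is also the level of each regression test. The Data analysis section states no level.
- Success on any one instrument counts as a positive primary result.
- The four test statistics share one common correlation, varied from 0 to 0.9.

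**Step 1. Reproduce the stated power.** Adding the losses gives 220 × (1 − 0.30) = 154 per arm. For a two-sample t-test with n per arm, the noncentrality is d × √(n/2), with 2n − 2 = 306 degrees of freedom.
- d = 0.3: 0.3 × √77 = 2.632. One-sided 5% critical value 1.650, power 0.837.
- d = 0.5: 0.5 × √77 = 4.387. Same critical value, power 0.997.

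Both stated figures are matched, but only with a one-sided test. Two-sided at 5% (critical value 1.968), power is 0.747 and 0.992. Compounding the losses instead gives 220 × 0.9 × 0.8 ≈ 158 per arm and one-sided power of 0.845 and 0.997, so 154 fits better.

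**Step 2. Chance of at least one false positive among four tests at 5%.** If independent: 1 − 0.95⁴ = 1 − 0.8145 = 0.185. For correlated tests, four equicorrelated normal statistics were simulated (2 million draws), counting draws in which any one exceeded its critical value.

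| Common correlation | Two-sided | One-sided |
|---|---|---|
| 0 | 18.5% | 18.5% |
| 0.3 | 17.4% | 16.4% |
| 0.5 | 15.6% | 14.4% |
| 0.7 | 13.0% | 12.0% |
| 0.8 | 11.4% | 10.6% |
| 0.9 | 9.4% | 8.8% |

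If the two SF-36 questions are scored separately there are five tests: 1 − 0.95⁵ = 22.6% if independent, and 14.9% at 0.7 (two-sided).

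**Step 3. Power when the 5% is divided over four tests.** 0.05 / 4 = 0.0125 per test, 154 per arm, with the noncentralities of step 1. Critical values at 0.0125 are 2.252 one-sided and 2.513 two-sided.

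| Effect size | Sides | Power at 0.05 | Power at 0.0125 |
|---|---|---|---|
| 0.3 | one | 0.837 | 0.648 |
| 0.3 | two | 0.747 | 0.548 |
| 0.5 | one | 0.997 | 0.983 |
| 0.5 | two | 0.992 | 0.969 |

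Comparisons should stay within a row. Setting 0.837 against 0.548 would mix the effect of dividing the level with a change from a one-sided to a two-sided test.

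**The case against.** **The multiplicity rule may be in an analysis plan that is not shown.** This is fair as far as a missing adjustment goes, and the point does not rest on that. It rests on two statements in the article that do not fit together. Which outcome the sample size is built on belongs in the protocol, and no later adjustment rule would make 0.837 the power of a test at a quarter of the level.

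**The primary measure may mean the quality-of-life domain.** That reading is possible, since the domain is the only one listed as primary, so the wording is ambiguous rather than plainly contradictory. But no composite is defined and each measure has its own regression, so the domain has no single test to which the stated power could belong.

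**The error rate depends on conditions the article does not give.** This stands. The Background speaks of weighing trade-offs between effects, which could mean reading the results as a profile. The four scores come from the same people and the same domain, so independence is an upper limit. The rate has to be given as a conditional range.

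**The power loss may be overstated.** In part. At an effect of 0.5 it is negligible. Holm's procedure is never less powerful than the plain Bonferroni split used here. The planned regression also adjusts for the T0 score: if the T0–T2 correlation were 0.4 to 0.6 (an assumption), the effective size at d = 0.3 would be 0.3 / √(1 − r²) = 0.327 to 0.375, and two-sided power at 0.0125 would be 0.64 to 0.78. The article's own effect-size figures match an unadjusted t-test, so that is the basis for comparison.

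**Two further inferences are not supported.** A reader might conclude that the SF-36 question about change over one year does not belong among the primary outcomes, because at T1 it mostly covers time before inclusion. The outcome regression, however, uses T2, 12 months after inclusion, where the recall period matches follow-up. A reader might also count the t-tests for change over time as extra primary tests, but that sentence does not describe a comparison between groups.

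**Conclusion.** The point holds as a mismatch: four unranked primary instruments, each with its own T2 regression, against a power claim for one unnamed measure.

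The consequence for false positives is conditional. With 5% per test and any single success sufficient, the rate runs from 18.5% (independent) through about 13% (correlation 0.7) to about 9% (correlation 0.9). It exceeds 5% at every correlation examined. A reader might infer that the trial has a fixed false positive rate of 13% to 19%; the article supports no such figure, because it gives no success rule, no correlations and no level for the regression tests.

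The consequence for power is firmer, because the article's own figures can be reproduced. They apply to one test at the full 5%. Divided over four, power at the small effect is no longer at the level the article calls sufficient, while at the larger effect it remains high. The matter is worth correcting before analysis but does not undermine the design.

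**What to change.** Before analysis, do one of the following.

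1. Name one instrument at T2 as the sole primary outcome, make the other three secondary in Table 1, and name that instrument in the Power calculation section. Which instrument is for the sponsor to decide; the article gives no ground for preferring one. If the SF-36 entry is chosen, state which question or score is meant.
2. Keep all four as primary, apply Holm's procedure to the four T2 group coefficients, say how the two SF-36 questions form one score, and restate the power at that level.

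In either case, state whether the test is one-sided or two-sided.

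The cost is wording only; no extra data or participants are needed. The drawback of the first option is that three instruments lose primary status. Under the second, fewer results will be nominally significant and the power quoted at an effect of 0.3 will be less favourable.

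### The t-test powers of 0.997 and 0.837 match an undisclosed one-sided 5% test; unadjusted two-sided power at d = 0.3 is about 0.75

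*Protocol article*

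**What the plan says.** In the Power calculation section the planned size is "We will include 220 elderly in both the experimental and control group". Attrition is given in two steps: "We expect a 10% loss to follow-up" between inclusion and T1, then "a 20% loss between T1 and T2".

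Two standardised effects follow: "Assuming an average effect size of 0.5 and significance of 5%, this gives a power of 0.997", and then "If we assume a small effect size of 0.3 with a significance of 5%, this still supplies sufficient power at 0.837". Two regression powers complete the paragraph: "At an average effect size (f2) of 0.15 and significance of 5%, assuming five independent variables, the power is 0.97" and "Even with 15 independent variables, the power remains sufficient at 0.856".

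The paragraph does not say whether the 5% is one- or two-sided, how many participants per group the powers refer to, or what level of power counts as sufficient. The Data analysis section plans t-tests and, for each measure, a regression of the T2 score on the T0 score, research group and demographic variables. It gives no direction for any test. The Aim section asks what the effects of the model are, without predicting a direction for the comparison.

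**The concern.** A reader who meets a 5% significance level with no further qualification will take it as two-sided. On that reading 0.837 at d = 0.3 is too high for the sample expected at T2. The figure matters because it is the article's assurance that even a small effect on quality of life would probably be found. Anyone interpreting a null result would rely on it. If it holds only for a one-sided test, the article should say so and justify the choice; otherwise the number should be the two-sided one.

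**Working it through.** **Inputs (Power calculation section).** 220 per group; losses of 10% and then 20%; significance 5%; d = 0.5 with stated power 0.997; d = 0.3 with stated power 0.837; f² = 0.15 with stated powers 0.97 (5 predictors) and 0.856 (15 predictors).

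**Retained number at T2.**
- Losses added: 220 × (1 − 0.30) = 154 per group.
- Losses compounded: 220 × 0.9 × 0.8 = 158.4, so 158 per group.

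**Formula.** For a two-sample t-test with n per group, df = 2n − 2 and the noncentrality is δ = d × √(n/2). Power is the probability that a noncentral t with these parameters exceeds the critical value (in either tail, for the two-sided test).

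**Reproducing the stated figures, n = 154, df = 306.**
- d = 0.5: δ = 0.5 × √77 = 4.387.
- d = 0.3: δ = 0.3 × √77 = 2.632.
- One-sided 5%, critical value 1.650: power 0.9969 and 0.8369. These round to the stated 0.997 and 0.837.

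**Is 154 the number used?** The regression powers give a separate check. With noncentral F and λ = f² × N, N = 154 gives 0.971 (5 predictors) and 0.856 (15 predictors), as stated. N = 158 gives 0.975 and 0.868. All four figures therefore point to 154. (In the regression, 154 is the size of one group only; that is a separate matter and makes those two powers conservative.)

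**Could a two-sided test give the pair?** No.
- 0.997 at d = 0.5 needs 175 to 182 per group, where power at d = 0.3 is 0.799 to 0.814.
- 0.837 at d = 0.3 falls between 193 per group (0.8364) and 194 (0.8383), where power at d = 0.5 is 0.998.
- The T1 sample, 220 × 0.9 = 198 per group, gives 0.999 and 0.846.

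**Two-sided 5% at the expected T2 sample, unadjusted.**

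| n per group | d = 0.3 | d = 0.5 |
|---|---|---|
| 154 | 0.747 | 0.992 |
| 158 | 0.7575 | 0.993 |
| Stated | 0.837 | 0.997 |

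At n = 154 and d = 0.3 the type II error is 1 − 0.747 = 0.253, against the implied 1 − 0.837 = 0.163, a ratio of 1.55. Two-sided power of 0.80 at d = 0.3 needs about 176 per group at T2.

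**Allowing for T0 adjustment.** If T0 and T2 scores correlate at r, adjustment multiplies δ by 1/√(1 − r²). The article gives no r, so the values below are assumptions. Two-sided 5%, d = 0.3, n = 154, no allowance for clustering:
- r = 0.3: δ = 2.632/0.954 = 2.76, power 0.79.
- r = 0.4: δ = 2.632/0.917 = 2.87, power 0.82.
- r = 0.5: δ = 2.632/0.866 = 3.04, power 0.86.

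**The case against.** The strongest reply is that nothing was computed wrongly. The article never says two-sided, and its figures are correct for a one-sided 5% test. The project's aim is to improve care, so a one-sided calculation is not out of character. This stands in part: the fault is an undisclosed test direction behind a stated power. An aim to improve care is not a directional hypothesis, however, and the research question is open.

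It can also be said that sufficient power is never defined, so 0.75 contradicts no threshold in the article. That is right; 0.80 is the customary benchmark, not the article's.

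A third reply is that the planned regression adjusts for T0, so the unadjusted t-test is not the main analysis. This limits what can be concluded. A reader might infer that the trial will miss a small effect one time in four. The documents do not support that. The 25% belongs to the unadjusted t-test, and with an assumed r of about 0.4 or more the adjusted analysis exceeds 0.80 before clustering. But the stated 0.837 does not rest on that adjustment either: it reproduces without any correlation, and none is given. Clustering within practices would pull power down, and the article gives no figure for it.

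A reader might also argue that two-sidedness is settled by the Background's interest in trade-offs between effects, or by the Data analysis sentence "To determine changes over time, t-tests will be performed for each process and outcome measure". Neither settles it. The first concerns breadth of evaluation across outcomes; the second concerns change over time and names no direction.

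**Conclusion.** The concern holds as a correction to a stated figure. The two t-test powers correspond to a one-sided 5% test with 154 per group, and the article does not disclose this. Under the conventional two-sided test the unadjusted power at d = 0.3 is 0.75 to 0.76, about 8 to 9 percentage points below the stated 0.837 and below the usual 0.80. At d = 0.5 it stays at 0.99, so the claim for an average effect is unaffected.

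The conclusion rests on two conventions that the article does not state: that an unqualified 5% is two-sided, and that 0.80 is the benchmark. It also rests on the article's own attrition; with all 220 per group retained, two-sided power at d = 0.3 would be 0.88. It does not show that the planned T0-adjusted analysis is underpowered, since that depends on a correlation and a clustering allowance the article does not give. The point should be corrected, but it is not a critical flaw.

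**What to change.** Restate the two t-test powers as two-sided 5%: 0.75 to 0.76 at d = 0.3 and 0.99 at d = 0.5. Give the retained number per group at T2 (154 if the losses are added, 158 if compounded). Stop describing the unadjusted power at d = 0.3 as sufficient.

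If the small-effect claim is to rest on the T0-adjusted regression, state the assumed T0–T2 correlation and the resulting power, and say whether clustering has been allowed for.

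If a one-sided test was really intended, declare it and justify it against the open research question.

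The cost is two corrected numbers and a sentence or two. Recruitment, design and analysis are unchanged; the stated power for a small effect becomes less favourable.
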